#### Phase 2: Feedback Report, Clinical Session, and Feedback Surveys

After the EMA period, a feedback report is shared with the mental health professional to be discussed during a regular therapy session. The report contains person-specific data on (1) general psychological functioning (ie, emotions and cognitions) and contextual information (eg, distribution of time alone vs with others face-to-face or on the web and activities in daily life); (2) the course of NSSI thoughts, NSSI urges, self-efficacy to resist NSSI, and NSSI behavior; and (3) the occurrence and intensity of other self-damaging thoughts and behaviors during the 28-day monitoring period. The section on general functioning includes pie charts displaying the proportion of time that someone spends across different contexts and box plots showing the median and variability of emotional and cognitive states. The section on NSSI provides information on the distribution and single-day average of NSSI thoughts, urges, and self-efficacy to resist NSSI (box plot and time series graphs). For example, high-risk days are operationalized as days on which the single-day average urge of NSSI is high (ie, mean response between 5-7 on a 7-point scale), coupled with low single-day average self-efficacy to resist NSSI (ie, mean response between 1-3 on a 7-point scale). In addition, the frequency of NSSI behaviors and types of methods are described, and NSSI urges are visualized across different situational, activity, and social contexts (bar charts). We also provide information about the occurrence of other self-damaging behaviors during the 28-day monitoring period. If the enrolled mental health professional cannot discuss the EMA feedback report (eg, because of treatment dropout or organizational issues), the patient can decide to have this session with another mental health professional or a clinical psychologist from the research team.

After the clinical session, an email is sent containing a link to a survey that assesses patients’ and mental health professionals’ experience of EMA and their perspectives on the EMA feedback report (Table 4). In case of nonresponse, 2 weekly reminders are sent. At this initial stage, we explore intrapersonal (ie, self-reflection and insight, self-efficacy, and subjective experiences) and interpersonal changes (ie, working alliance and helpful aspects during the clinical session) associated with the experience of EMA and the use of the EMA feedback report in treatment. The feedback survey also includes open questions assessing attitudes about self-monitoring, the content of the items, the feasibility of EMA, and the potential of EMIs for NSSI and other self-damaging behaviors (Table 4).

**Table 4 table4:** Overview of constructs assessed in the feedback survey.

Survey battery	Measure and example item	Source	Items, n; response scale
Self-insight and reflection in general^a^	Adapted Self-Reflection and Insight Scale: “The self-monitoring made me more aware of my feelings and thoughts”	Original [116] and Dutch translation: FBT^b^	8; 6-point Likert scale
Self-efficacy in general	Adapted Self-Efficacy Scale: “By what I learned about myself through the self-monitoring, I feel that I am better able to solve difficult problems if I try hard enough”	Original [99] and Dutch translation [100]	10; 4-point Likert scale
Self-insight and reflection with respect to NSSI^c^ and other self-damaging behaviors^a^	Adapted Self-Reflection and Insight Scale: (1) experience of EMA^d^: “The self-monitoring made me more aware of my triggers for self-injury” and (2) use of EMA in therapy: “Discussing the monitoring results together with my clinician made me more aware of my triggers for self-injury”	Original [116] and Dutch translation: FBT	10; 6-point Likert scale
Self-efficacy resisting NSSI and other self-damaging behaviors	Adapted Self-Efficacy Scale: (1) experience of EMA: “By what I learned about myself through the self-monitoring, I now know better what to do when I am experiencing an urge to self-injure” and (2) use of EMA in therapy: “By discussing the monitoring results together with my clinician, I now know better what to do when I am experiencing an urge to self-injure”	Original [99] and Dutch translation [100]	10; 4-point Likert scale
Effect of discussing EMA results in therapy on the working alliance^a^	Adapted Working Alliance Inventory (short version): (1) task: “Discussing the results together helped us to understand which changes I need to make,” (2) bond: “I feel my clinician understands me better because of the monitoring results,” and (3) goal: “Discussing the results together makes me feel we are both working toward the same goals in therapy”	Original [117] and Dutch translation: FBT	12; 6-point Likert scale
Helpful aspects during clinical session^a^	Questions assessing any helpful or hindering aspects of the session and experience of clinician and therapeutic session as engaging and supportive, open and authentic, empathic, explorative, confrontational, and making positive progress: “I believe that my problems can be addressed through therapy”	Original [118] and Dutch translation [119]	40; mixed
Subjective experiences of EMA	Questions assessing (1) negative experience: “The self-monitoring questions caused me stress,” (2) positive experience: “I enjoyed the self-monitoring,” (3) learning experience: “I would describe the self-monitoring as a learning experience,” and (4) facilitates self-regulation: “The self-monitoring questions helped me to structure my thoughts”	Self-developed	12; 5-point Likert scale
Expectations of feedback and compensation	Questions assessing the overall and relative importance of receiving study findings, personal feedback, and financial compensation	Items from Kiekens et al [19] and self-developed	11; mixed
Qualitative feedback	Questions assessing attitudes about self-monitoring, content of the items, length of questionnaires, experience and feasibility of self-monitoring, utility and potential effect on the therapy process, and utility and scope of future interventions	Self-developed	10; open questions

^a^Clinician version also included these questions.

^b^FBT: forward-backward translation.

^c^NSSI: nonsuicidal self-injury.

^d^EMA: ecological momentary assessment.

#### Phase 3: Follow-up Surveys After 1 and 3 Months and (Optional) Interviews About Experiences and Attitudes Toward EMA and EMIs

Phase 3 includes 2 brief web-based follow-up surveys after 4 and 12 weeks and an optional interview. The surveys assess past-week psychological distress and the presence of NSSI and other self-damaging behaviors since completing the self-monitoring (first survey) or between the follow-up surveys (second survey; see questionnaires indicated with subscript in Table 1). In case of nonresponse, 2 weekly reminders are sent. The qualitative interviews assess more in depth the experiences of using EMA and the utility, content, and design of future EMIs for NSSI among a voluntary subsample of individuals seeking treatment (online after the feedback session) and mental health professionals (on site after they have participated with at least 2 patients in the study). The interview guides can be consulted on the project’s Open Science Framework (OSF) page [115].

##### Participant Incentives and Engagement

Participants are recognized as valued contributors to the research and receive financial incentives, information about the overall findings, and feedback on their data. Patients are financially compensated via a structured financial scheme when (1) the feedback survey (if the EMA report was discussed) and (2) at least 1 of the follow-up surveys are completed: €35 (approximately US $38) if compliance with the monitoring protocol is >33% (or >55 EMA surveys), €70 (approximately US $76) if compliance is >65% or (>109 EMA surveys), and €100 (approximately US $109) if compliance is >83% (or >139 EMA surveys). Otherwise, patients receive €20 (approximately US $22) in financial compensation. In addition, personalized feedback reports are provided so that relevant information can be fed back into the therapy room. Patients can also opt in to receive updates on the general findings of the project. Finally, mental health professionals receive €10 (approximately US $11) as compensation for completing the feedback survey after the clinical session in which they discuss the EMA feedback report. We do not provide a financial incentive for participation in the interviews (phase 3).

##### Research Training and Well-being

All research activities are performed by clinically trained research staff. Risk monitoring of people who frequently self-injure requires good-quality training in working with individuals who engage in NSSI and are at increased risk for suicide [19]. Therefore, research staff who interact with participants and are part of the risk-monitoring team are licensed clinical psychologists who have received additional training that covered how to support participants during an acute suicidal crisis. In addition, although there is a psychologist *on call* outside of office hours, responsibility is always shared with the first and second authors (GK: PhD level and good clinical practice certified and LC: PhD level and cognitive behavioral therapist), who are available for supervision by telephone during recruitment hours. Finally, there are regular debriefings to ensure the well-being of all team members throughout the study’s data collection period.

### Statistical Analyses

#### Overview

The psychometric properties of baseline measures (eg, Cronbach α), EMA multi-item scales (eg, multilevel reliability [120]), and interrater reliability of diagnostic interviews (a subset of 20% of the sample, approximately 24 participants) will be reported. To accommodate the hierarchical structure of the EMA data (eg, observations nested within individuals), our 3 primary aims will be analyzed by using a combination of statistical techniques. First, descriptive statistics (eg, means, modes, SDs, intraclass coefficients, and correlations) will be used to describe the sample in terms of baseline characteristics; compliance rates; presence; comorbidity patterns; and moment-to-moment variability of NSSI outcomes across minutes, hours, days, and weeks. Second, we will use dynamic structural equation modeling (DSEM), which integrates three modeling approaches [121,122]: (1) time series analysis, which allows for modeling the lagged relation between repeated measures in a single participant; (2) multilevel modeling, which takes the higher-order data structure into account and models these relationships for multiple participants while capturing variability within and between persons over time; and (3) structural equation modeling, which takes measurement error into account and allows for multiple outcome variables, latent variables, and mediation effects [123].

Using DSEM will clarify the extent to which momentary factors at time point *t*_–1_ (eg, negative affect) predict NSSI thoughts, NSSI urges, self-efficacy to resist NSSI, and NSSI behavior (or other self-damaging behaviors) at time point *t*, above and beyond the lagged version of the outcome variable (ie, the autoregressive parameter) and confounding variables at time point *t*_–1_ (eg, NSSI urges in the prediction of NSSI behavior). We will attempt to include random intercepts (predictors and outcomes) and random slopes (predictors) for momentary variables, with an unrestricted correlation structure if models converge (the maximum number of iterations is 50,000 by default). The time interval (Tinterval) statement will account for unequally spaced intervals owing to missing data and random sampling within blocks, with missing data handled using a Kalman filter approach [122]. Given that all participants have a recent history of NSSI but do not necessarily engage in other self-damaging behaviors, models that investigate within-person associations with disordered eating, substance use, and STB will be based on a subsample of participants that show variation in these secondary outcomes.

Third, we will use group iterative multiple model estimation (R package *gimme* [124]) to assess between-person variability in risk associations. Group iterative multiple model estimation estimates a unified structural equation model that includes lagged and contemporaneous relations in a network model [124,125] and accurately recovers group-, subgroup-, and individual-level associations in time series data. Fourth, fully idiographic modeling will be applied based on each participant’s time series data to identify the most relevant factors for each individual without overfitting models [126,127]. Elastic net regularization will be used as a statistical classification approach, which produces sparse models through coefficient penalization with k-fold cross-validation (R package *glmnet* [128]). Fifth, survival analysis will be used to investigate the factors that predict the transition from intense NSSI urges to behavior [129]. Importantly, however, as the analysis of intensive longitudinal data is a burgeoning field, newly available methods will also be considered (eg, continuous-time and Markov switching models [130-133]).

Finally, the secondary objective will be analyzed using a mixed methods approach. We will use thematic analysis to evaluate open-ended questions and interview data regarding end users’ experiences and perspectives [134]. Quantitative questionnaire data will be analyzed using descriptive statistics and regression analyses to explore associations with demographic and clinical characteristics.

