**Block C: NSSI^b^ (4-5 items)**					
	Retrospective thoughts	“Since the last beep, have you considered deliberately hurting yourself without wanting to die?”		7-point scale (ranging from not at all to very much)	
	Momentary urge	“Right now, how strong is the urge present to hurt yourself without wanting to die?”		7-point scale (ranging from absent to very strong)	
	Retrospective behavior	“Since the last beep, have you deliberately hurt yourself without wanting to die (for example, cut, scratched, or hit yourself)?”		(a) No, (b) yes	
	Retrospective behavior (method)	(If b): “How have you self-injured?”		(a) Cutting or carving, (b) scratching, (c) hitting, (d) burning, (e) biting, (f) head banging, (g) wound interfering, (h) other method (describe briefly)	
	Momentary self-efficacy to resist	“Right now, how confident are you that you can resist engaging in NSSI?”		7-point scale (ranging from not at all to very)	

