#### Expected Sample Size

We intend to recruit 120 individuals seeking treatment. Analyses that include 100 to 120 participants will yield sufficient statistical power (≥0.80) to detect within-person effects as small as 0.07 to 0.09 in multilevel autoregressive models. These power calculations were conducted using Monte Carlo simulations with the following conservative estimates [135]: a 1:0.67 ratio of random intercept to within-person residual deviation, a 1:0.25 ratio of random intercept to random slope SD, first-order and slope-intercept correlations of 0.5, and compliance of 60% to the regular EMA surveys. Recent studies have used pooled machine learning models with fewer observations and participants [127]. In addition, it has been shown recently that as few as 60 assessments from 25 individuals allow robust estimation of general, shared, and person-specific temporal associations in intensive longitudinal data [136].

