Fourth, we operationalize NSSI and other self-damaging behaviors comprehensively (ie, thoughts, urges, and behavior) and assess a broad range of theoretically relevant factors (emotions, cognitions, contextual information, and social appraisals); however, as a consequence, most constructs rely on single EMA items that were selected from prior EMA studies or modified from conventional survey questionnaires to keep the workload for participants under control [141]. However, against the backdrop of a lack of psychometrically validated items for assessing psychological constructs with EMA [142] and a need to develop standardized measures [143], we will calculate the multilevel reliability of composite constructs (eg, negative affect) and made all EMA items (for the original Dutch items see the OSF page) publicly available [107]. Fifth, we provided additional (shorter) EMA surveys when participants report intense NSSI urges and contact participants and clinical staff when there is an increased suicide risk, which might result in underreporting of NSSI urges and STB. Sixth, because all participants receive mental health treatment, there might be structural changes in the descriptive patterns of self-damaging thoughts and behaviors across the monitoring period. We will evaluate this, and if the assumption of stationarity is violated, we will include days since study enrollment as a covariate for the outcome under investigation. Finally, we may miss moments leading up to self-damaging behaviors in the late evening and overnight as no EMA surveys are scheduled after 10 PM. Although we can assess to what extent this is the case for NSSI behavior (as people could register self-injury via the push button in the m-Path app), future research might benefit from sampling schemes adapted to people’s sleep and wake-up times.

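### The plan credits its model with handling measurement error, but the NSSI outcomes are single items with no error term described, so lagged effects of co-occurring factors can be spurious

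*Protocol article*

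**What the plan says.** In Statistical Analyses, Overview, dynamic structural equation modeling (DSEM) is introduced as combining three approaches, one of them "structural equation modeling, which takes measurement error into account". The same section sets the test for prospective effects. A factor at t-1 must predict the outcome at t "above and beyond the lagged version of the outcome variable (ie, the autoregressive parameter", and also beyond confounders at t-1. The example given is "NSSI urges in the prediction of NSSI behavior".

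Table 2, Block C shows how the NSSI outcomes are measured. Urge is one 7-point item ("Right now, how strong is the urge present to hurt yourself without wanting to die"), and thoughts and self-efficacy are also one 7-point item each. In Block A, rumination, self-criticism, loneliness and emptiness have one item each, while negative affect has five and positive affect two. Limitations acknowledges that "most constructs rely on single EMA items that were selected from prior EMA studies" or adapted from questionnaires. Multilevel reliability is planned only for multi-item scales (Overview) and composites (Limitations). The power inputs in Expected Sample Size contain no reliability.

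**The concern.** Structural equation modeling corrects for measurement error only when a construct has several indicators or the model has an explicit error term. No continuous NSSI outcome has several indicators. The Overview describes random effects, unequal intervals and missing data, but no error term for single items. A reader could therefore conclude that the problem has been dealt with.

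At stake is what the lagged test means. Objectives asks whether NSSI thoughts, urges and self-efficacy predict each other prospectively, and which emotions and cognitions act as risk or protective factors. A noisy lagged outcome adjusts incompletely for the prior level. A factor that is high only because urges are already high can then look like an antecedent. The study exists to tell these two apart, and its results are meant to inform real-time interventions.

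**Working it through.** **Inputs from Expected Sample Size:** N = 100 to 120, residual SD 0.67 and random slope SD 0.25 (both relative to a random intercept SD of 1), first-order correlation 0.5, compliance 60%. From the sampling design: 28 days × 6 = 168 surveys. At 60% that is about 101 completed, with 28 × 5 × 0.6² ≈ 50 adjacent same-day pairs.

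**Assumptions, not in the documents:** two-sided alpha 0.05; within-person reliability of the outcome item (ry) and of the factor (rx); concurrent within-person correlation (rho); predictor variance (Vx).

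**1. The plan's own figure.** The article claims power of at least 0.80 to "detect within-person effects as small as 0.07 to 0.09 in multilevel autoregressive models". Detectable effect = (1.96 + 0.84) × √(0.25²/N + 0.67²/(N·T·Vx)), with T = 50 to 101 and Vx = 0.25 to 1. This gives 0.066 to 0.080 at N = 120 and 0.073 to 0.088 at N = 100, so the stated 0.07 to 0.09 is reproduced.

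**2. Coefficient of a factor with no lagged effect.** Regress the observed outcome at t on the observed outcome and factor at t-1, with true autoregression phi. The large-sample standardized coefficients are:
- factor: b = phi·rho·√(rx·ry)·(1 − ry) / (1 − rho²·rx·ry)
- autoregression: a = phi·ry·(1 − rho²·rx) / (1 − rho²·rx·ry)

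Base case phi = 0.5, rho = 0.5, rx = 0.8, ry = 0.7:
- b = 0.5 × 0.5 × √0.56 × 0.3 / (1 − 0.25 × 0.56) = 0.0561/0.86 = 0.065
- a = 0.5 × 0.7 × 0.8 / 0.86 = 0.28/0.86 = 0.33, against a true 0.50

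At ry = 1, b is 0.

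**3. Range.** With ry = 0.6, 0.7, 0.8; rx = 0.8; and rho and phi each 0.3 to 0.6 in steps of 0.1 (48 cells), b runs from 0.015 to 0.12. The median is 0.048, and 10 of the 48 cells reach 0.07.

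Step 2 reads 0.5 as the true autoregression. If it is instead the observed autocorrelation, and rho of 0.3 to 0.5 is also observed, b is 0.071 to 0.143 at reliability 0.7, 0.041 to 0.083 at 0.8 and 0.018 to 0.037 at 0.9 (equal reliabilities).

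**4. How often it would be called an effect.** With T = 50 and Vx = 1, SE = √((0.25² + 0.67²/50)/N) = 0.0267 at N = 100 and 0.0244 at N = 120. Dividing 0.065 by these would give rejection in 68% to 76% of studies, but it mixes a standardized bias with raw-scale SDs. A residual SD of 0.67 implies a within-person outcome SD of 0.67/√(1 − 0.33²) ≈ 0.71 to 0.67/√(1 − 0.5²) ≈ 0.77. The bias on that scale is 0.065 × 0.71 ≈ 0.046 to 0.065 × 0.77 ≈ 0.050, and rejection is about 41% to 54% instead of 5%.

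**5. Simulation** (N = 120, 168 surveys, 60% compliance, phi 0.5, equal reliabilities, only 30 runs per cell). Rejection of a true null:

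| rho | reliability | slope SD 0.25 | no slope variation |
|---|---|---|---|
| 0.5 | 0.7 | 67% | 100% |
| 0.5 | 0.8 | 40% | 93% |
| 0.3 | 0.8 | 7% | 57% |
| 0.3 to 0.7 | 1.0 | 7% | 0 to 3% |

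**6. Does an error term help?** A latent autoregressive state plus error variance, fitted to single items in 8 simulated data sets (reliability 0.7, rho 0.5), moved the mean spurious cross-lag from 0.056 to −0.002. Single runs ranged from −0.06 to 0.05. In a further 15 data sets the unstandardized cross-lag fell from 0.076 to 0.015, the autoregression rose from 0.34 to 0.49, and the SE went from 0.016 to 0.019.

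**The case against.** The sentence in the Overview describes a general capability. In full it reads "structural equation modeling, which takes measurement error into account and allows for multiple outcome variables, latent variables, and mediation effects", and nobody would take it to promise mediation in every model. Nothing in the article rules out an error term, and single items do not prevent one, because an autoregressive series with separate error is identifiable when carry-over is not near zero. The Open Science Statement says analysis plans and code will be posted. Limitations openly discloses the single items and gives participant workload as the reason.

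Much of this stands. A reader might infer that the plan excludes error correction, or that null predictors will be credited with effects as large as those the study is powered for. The documents support neither. The first reads silence as a decision. The second rests on reliabilities and correlations that the article does not give, and most of the grid lies below 0.07.

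The coverage is also limited. Several directional hypotheses concern NSSI behavior, which is binary and was not computed here. Being alone is a categorical report, not a noisy rating.

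The error model has its own weakness. At about 2-hour spacing it separates persistent from non-persistent variance and cannot tell error from a genuine brief urge. The article itself describes NSSI thoughts as short-lived.

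What remains is a stated advantage of the method that the measurement design does not deliver for the continuous NSSI outcomes without a step the article does not describe.

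**Conclusion.** The point holds as a conditional one. If observed single items serve as the lagged outcome, a factor that only co-occurs with a continuous NSSI outcome can receive a spurious standardized lagged coefficient of about 0.015 to 0.12, median about 0.05. This assumes outcome reliability of 0.6 to 0.8, factor reliability of 0.8, and concurrent correlation and autoregression of 0.3 to 0.6. Comparison with 0.07 to 0.09 is itself an assumption, because the article does not state the scale of that figure. In the base case the false positive rate is about 41% to 54% and the autoregressive parameter reads 0.33 instead of 0.50. At the favorable end (correlation 0.3, reliability 0.8, slopes varying) the simulated rate was 7%, close to nominal. The direction of the bias follows from the algebra; its size in this study is unknown. Modeling negative affect as a latent factor would not repair it, because the error that matters most is in the lagged outcome.

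**What to change.** In Statistical Analyses, Overview:
- Limit the measurement-error statement to constructs with several indicators, for example negative affect as a 5-indicator within-person factor.
- For cross-lagged claims on single-item continuous outcomes, keep the planned model as the main model and prespecify a sensitivity analysis beside it. Use a latent autoregressive state plus error variance where this is estimable; otherwise fix reliability at 0.6, 0.7 and 0.8.
- Report a factor as a prospective predictor beyond the prior level only together with a statement of whether the effect survives that analysis.

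The cost is extra model runs, wider intervals and possible non-convergence. No new data are needed. Because the error term may absorb genuine short-lived fluctuation, the error model should not replace the main model.

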Guided by contemporaneous models of NSSI [33-35] and emerging work [36-38], we will evaluate contextual information, social appraisals, emotions, and cognitions as within-person risk and protective factors for cognitive and behavioral NSSI outcomes. We hypothesize that the risk of NSSI behavior will be higher when people are alone [30], after situations characterized by negative social appraisals and perceived conflict [39,40], and after increased negative and decreased positive affect [41]. Given that specific emotions may incrementally predict higher risk (eg, feeling stressed) [30,42] or protect more strongly against NSSI (eg, feeling relaxed) [27], the findings will also be analyzed using specific emotions as units of analysis. On the basis of the benefits and barriers model of NSSI [34,43], which argues for a unique role of self-critical thoughts in explaining NSSI behavior, we will evaluate the association between momentary fluctuations in self-critical thinking and NSSI urges and NSSI behavior. Building upon the emotional cascade model [35,44], which posits that reinforcing cyclic cascades between rumination and negative affect form a dynamic process in which self-injury is suggested to break this cycle by distracting from rumination, the utility of momentary ruminative thinking and the interplay with negative emotions in predicting NSSI behavior will be investigated. However, because the relevance of these theoretically inspired within-person risk factors for NSSI might differ between individuals [45,46], we will also determine variability in individual risk associations.

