A second primary objective is to advance understanding of the transition from NSSI thoughts and urges to NSSI behavior. Although existing theoretical models of NSSI do not distinguish between NSSI thoughts or urges and NSSI behavior, contemporary “ideation-to-action” theories of suicide explicitly make this distinction [47] and suggest that the factors that lead to suicidal thoughts or urges are not necessarily the same factors that lead to behavior (ie, suicide attempts). Emerging evidence indicates that incorporating ideation-to-action thinking might be equally relevant for NSSI. For instance, preliminary work suggests that previously identified risk factors for NSSI behavior (eg, emotional factors) might uniquely predict NSSI thoughts but not the occurrence of NSSI behavior [27]. Inspired by the cognitive-emotional model of NSSI [33], we anticipate that momentary self-efficacy to resist NSSI will be a potent protective factor against NSSI behavior. People retrospectively report that the transition between NSSI thoughts or urges and NSSI behavior is typically <30 minutes [30,31], meaning that there might be a brief window of opportunity to intervene during these moments of acute risk for NSSI behavior. Therefore, in an attempt to inform and facilitate such intervention efforts, we will make a thought-to-action distinction and clarify the specificity of risk and protective factors to identify factors that increase or decrease the likelihood of transitioning from NSSI thoughts or urges to NSSI behavior in real time among individuals seeking treatment.

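### Urge at the previous survey is named as a confounder of NSSI behavior but may also be a consequence of affect, so the urge-adjusted coefficient alone does not test the Objective 1 behavior hypotheses and may understate them

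*Protocol article*

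**What the plan says.** **Hypotheses.** In the protocol article, Objectives, the first primary objective includes directional statements about behavior: "We hypothesize that the risk of NSSI behavior will be higher when people are alone", after negative social appraisals and perceived conflict, "and after increased negative and decreased positive affect". None is stated as conditional on the urge at the time. (For self-criticism and rumination the text promises only to evaluate associations.)

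**Transition.** The second primary objective is a different question: to "identify factors that increase or decrease the likelihood of transitioning from NSSI thoughts or urges to NSSI behavior in real time". In that context the article cites preliminary work in which emotional factors "might uniquely predict NSSI thoughts but not the occurrence of NSSI behavior".

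**Model.** Statistical Analyses, Overview, uses dynamic structural equation modeling (DSEM) to predict NSSI thoughts, urges, self-efficacy and behavior at t from momentary factors at t−1, "above and beyond the lagged version of the outcome variable (ie, the autoregressive parameter) and confounding variables at time point" t−1. The one example of such a confounder is "eg, NSSI urges in the prediction of NSSI behavior". Mediation is mentioned as something DSEM permits; no mediation model is described.

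**Timing.** In Table 2 affect and urge are both rated as of the moment of the survey. The item on NSSI thoughts instead covers the time since the last beep.

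**The concern.** A confounder should not itself be changed by the factor under study. Here one sentence places urge on both sides: as an outcome that negative affect may predict, and as a confounder to be held fixed when affect predicts behavior. Because affect and urge are recorded together, urge at t−1 may already carry part of whatever the affect at t−1 does.

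Holding urge fixed asks whether affect adds anything given the urge already present. That is close to the second objective. The first objective asks whether behavior is more likely after certain states, whatever the urge. If the adjusted coefficient were the only one reported, a null could be read as no relation between affect and NSSI behavior when the relation runs partly through urge.

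**Working it through.** **1. The plan's own figure.** The article gives no number on this point. The nearest is the detectable within-person effect of 0.07 to 0.09 (Expected Sample Size). It can be approximated by detectable effect = (1.96 + 0.84) × √[(slope SD² + residual SD²/(T × Var X))/N], with slope SD 0.25 and residual SD 0.67 (the stated ratios, intercept SD set to 1). T is 168 × 0.60 = 100.8 answered surveys, or 28 × 5 × 0.60² = 50.4 consecutive within-day pairs. Two-sided alpha of 0.05 and Var X of 0.25 to 1 are assumptions; the stated correlations of 0.5 are not modelled.

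- N = 100, T = 100.8, Var X = 1: 2.80 × √[(0.0625 + 0.0045)/100] = 0.0725.
- Over all settings: 0.0725 to 0.0878 at N = 100, and 0.0662 to 0.0801 at N = 120.

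The figure is reproduced. It does not bear on this point: it describes multilevel autoregressive models with a residual deviation, and no binary outcome is stated.

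**2. How much of the affect coefficient could urge at t−1 absorb?** The documents give no path values, so every value below is assumed. Let A be affect, U the urge reported at the survey, M the urge between surveys that immediately precedes behavior, and B behavior:

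- A(t) = 0.4·A(t−1) + g·U(t−1) + 0.8·noise
- U(t) = a0·A(t) + 0.3·U(t−1) + 0.7·noise
- M(t) = φ·U(t−1) + a1·A(t−1) + 0.7·noise
- logit P[B(t) = 1] = −3.2 + M(t), giving behavior at about 5% of surveys

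B(t) was regressed (logit) on B(t−1) and A(t−1), with and without U(t−1), in one simulated series of 400,000 occasions per scenario. When g = 0, the coefficient with urge is about a1, and without urge about a1 + φ·s, where s is the slope of U on A at the same survey. With a0 = 0.5: Var A = 0.64/(1 − 0.16) = 0.762; Cov(U, A) = 0.5 × 0.762/(1 − 0.3 × 0.4) = 0.433; s = 0.433/0.762 = 0.568.

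| Assumed paths | a0, a1, φ, g | Approximation without / with urge | Simulated without / with urge | Kept |
|---|---|---|---|---|
| All through urge present at t−1 | 0.5, 0, 0.4, 0 | 0.227 / 0 | 0.233 / 0.010 | 4% |
| Mixed | 0.5, 0.2, 0.4, 0 | 0.427 / 0.2 | 0.432 / 0.209 | 48% |
| Mostly through urges arising after t−1 | 0.5, 0.4, 0.15, 0 | 0.485 / 0.4 | 0.475 / 0.391 | 82% |
| Wholly through later urges | 0.5, 0.4, 0, 0 | 0.4 / 0.4 | 0.387 / 0.384 | 99% |
| Mixed, and earlier urge drives affect | 0.5, 0.2, 0.4, 0.3 | – | 0.445 / 0.200 | 45% |
| Affect has no effect; earlier urge drives affect | 0, 0, 0.4, 0.3 | – | 0.029 / 0.004 | (true effect zero) |

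**3. Reading.** In the first five rows affect truly raises the risk of behavior, and adjustment keeps from 4% to 99% of the coefficient. In the last row the coefficient without urge is spurious, and adjustment removes most of it. The two coefficients answer different questions, and the documents do not say which row is nearest the truth.

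**The case against.** **Condensed article.** The adjustment is given only as an example, several techniques are listed for the three aims, and the analysis plan for each publication is promised on the Open Science Framework. Exact covariate sets may be left to such a plan, so models without urge are not excluded. This stands. But the one example given is the very pairing the behavior hypotheses concern, and no model without urge is described for them.

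**Urges are outcomes too.** A factor that raises urges should show in the urge model, and Objectives also asks how the NSSI outcomes predict each other. So the first objective as a whole would not miss such a factor. This stands, but the hypotheses at issue are about behavior.

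**Urge may be a true confounder.** Earlier urge can drive both affect and later behavior, and the order of two ratings in one survey is unknown. This stands, and it is why simply dropping urge is not a clean remedy.

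**A stronger reading not supported.** A reader might infer that the article's own theory has affect acting through urges, so that adjustment removes the main pathway. No section states such a chain; the article says that "existing theoretical models of NSSI do not distinguish between NSSI thoughts or urges and NSSI behavior". Moreover, only urge at t−1 is held fixed. Regular surveys are about 2 hours apart and the transition is reported as typically under 30 minutes, so urges arising after t−1 are not conditioned on.

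**Conclusion.** The point holds as a mismatch between hypothesis and named model. Calling urge at t−1 simply a confounder is not consistent with listing it as an outcome of the same factors, and the urge-adjusted coefficient alone does not test the unconditional behavior hypotheses. It may understate them by anything from almost nothing (99% kept) to almost everything (4% kept). That range rests wholly on assumed paths in a simple single-series illustration without between-person variation; it is not an estimate for this study.

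Two further inferences should be resisted. The coefficient without urge is not the pure total effect, since it may carry influence of urge on affect. And a binary-outcome coefficient should not be set against the detectable effect of 0.07 to 0.09, which is not stated for a binary outcome. The change is worth making because it uses data already collected and prevents a null adjusted coefficient from being reported as no risk association.

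**What to change.** For the behavior hypotheses under the first objective:

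- Report the lagged association adjusted for the lagged outcome and time terms, without urge at t−1, next to the urge-adjusted one. A lagged mediation model in DSEM is an alternative.
- Label the urge-adjusted coefficient as association given current urge, and tie it to the transition question of the second objective.
- State that the urge-adjusted model alone will not be used to conclude that a factor is unrelated to NSSI behavior.
- In Statistical Analyses, describe urge at t−1 as a possible confounder and a possible consequence of affect. Thoughts at t−1 may stay as a covariate, because that item looks back over the time since the last beep and so largely precedes the affect rating.

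Cost: one more model per predictor and two coefficients to explain. Each needs its caveat: the one without urge may include influence of urge on affect, and the one with urge may leave out part of what affect does.
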